### Sample size and recruitment

In this study, the primary outcome of the psychological pain score was selected to calculate the effect sizes. Based on the literature [20], the post-intervention psychological pain score measured using DT was 1.5 ± 0.98 for the experimental group and 2.3 ± 1.05 for the control group, with a statistically significant difference, and an effect size d of 0.788 was calculated. In the G*Power software, the number of participants in each group sample was calculated as 35 cases by using two independent samples t-test and taking bilateral α = 0.05 and 1-β = 0.9. Considering a dropout rate of 20%, the minimum sample size was therefore derived as 84 patients, 42 in each group.

Nurses will introduce the study to depressed inpatients who meet the inclusion criteria, and if a patient agrees verbally to participate, nurses will notify the researchers. The researchers will explain the information about the study in more detail to participants, discuss the appropriate timing of the intervention, and provide informed consent. Then, the participant will return the signed informed consent to the researchers. Participants will be recruited from June 2022 to June 2023, and once recruited, patients will be randomly assigned to the experimental or control group.

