### Data analysis

SPSS 25.0 will be used for statistical analysis of the data. All collected data will be processed for intention-to-treat analysis. ANOVAs and Chi-Square tests were performed to compare demographic and clinical variables, reasons for attrition, and baseline scores on primary and secondary outcomes between the groups, and significant imbalances between the two groups will be checked. Categorical variables will be explored using chi-square tests, and continuous variables will be analyzed using t-tests or Mann–Whitney U tests, thus exploring baseline differences between the two groups. The number of drop-outs and follow-up losses in both groups will be reported based on descriptive data.

This study will compare the differences in primary and secondary outcomes between the two groups at two time points: baseline and 2 weeks(post-intervention). The generalized estimating equation model (GEE) is a statistical model developed based on the generalized linear model, specifically designed to deal with repeated measures such as longitudinal data. Given the association between outcome variables at multiple time points for individuals in our study, the GEE model will be performed to compare the trends of primary and secondary outcomes at different time points (baseline, 1 week, 2 weeks, 1 month, and 6 months) in the two groups, adjusted for confounding factors of statistical differences in the baseline. The GEE model will be applied to explore the effects of time factors, intervention factors, and interactions between intervention factors and time factors on each variable between the two groups. When there is an interaction effect, then the analysis of the simple effects will be adopted. In this study, no subgroup analysis will be performed. To reduce the risk of type I errors, Bonferroni correction will be used for multiple comparisons, that is, dividing 0.05 by the number of comparisons. Thus, *P* < 0.01 represents a statistically significant difference.

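### The plan gives two routes to the 2-week group difference, one of them conditional on a five-visit interaction test, and does not say which decides the primary hypothesis

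*Protocol article*

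**What the plan says.** Sample size and recruitment: "the primary outcome of the psychological pain score was selected to calculate the effect sizes". The inputs are post-intervention scores of "1.5 ± 0.98 for the experimental group and 2.3 ± 1.05 for the control group", from which "an effect size d of 0.788 was calculated", and the number per group was found "by using two independent samples t-test and taking bilateral α = 0.05 and 1-β = 0.9". The Data collection section places post-intervention at 2 weeks.

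The Data analysis section gives two routes to the difference at that visit.

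- Direct, with no condition attached: "This study will compare the differences in primary and secondary outcomes between the two groups at two time points: baseline and 2 weeks(post-intervention").
- Through the GEE, fitted to baseline, 1 week, 2 weeks, 1 month and 6 months, with terms for time, intervention and their interaction: "When there is an interaction effect, then the analysis of the simple effects will be adopted".

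The section does not rank the two. It does not say what is concluded when no interaction is found. The Methods paragraph of the Abstract names the GEE, and no other method, for judging effectiveness. The Data analysis section ends by setting P<0.01 as the significance threshold.

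**The concern.** The sample size calculation supports a single-degree-of-freedom comparison at one visit. A group-by-time test over five visits asks a different question: whether the group difference changes anywhere across the schedule. Its power depends on the whole time course and on the within-patient correlation, and neither entered the sizing. If the 2-week difference may be read only after that test succeeds, a real effect of the planned size can go unreported because the interaction missed its threshold.

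The second problem is the choice itself. The same contrast has two routes with different pass rules. Unless one is named as decisive, the analyst can rely on whichever succeeds after seeing the data.

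**Working it through.** **1. The plan's own figure.** d = (2.3 − 1.5)/√[(0.98² + 1.05²)/2] = 0.788. An exact two-sample t-test at two-sided 0.05 has power 0.893 with 34 per group and 0.901 with 35, so the stated result, "the number of participants in each group sample was calculated as 35 cases", reproduces. With 42 randomised per group and 20% dropout, 42 × 0.8 = 33.6 completers per arm remain.

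**2. Assumptions the document does not supply.** Unit SD, no baseline difference, exchangeable correlation r of 0.3, 0.5 or 0.7, time categorical, and d = 0.788 at 2 weeks. Two profiles over 1 week, 2 weeks, 1 month and 6 months:

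- sustained: 0.788 at all four visits;
- fading: 0.394, 0.788, 0.591, 0.394.

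**3. The direct contrast.** The normal approximation gives 0.788 × √(33.6/2) = 3.23 standard errors, hence power 0.90 at 0.05.

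**4. The interaction test.** The vector of five group differences has covariance (2/n)[(1−r)I + rJ]. The 4-df Wald statistic then has noncentrality n/[2(1−r)] × Σ(δₜ − δ̄)², with the baseline δ equal to 0. At r = 0.5 the multiplier is 33.6.

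- Sustained: δ̄ = 0.6304, sum of squares 0.4968, noncentrality 16.7, power 0.92.
- Fading: δ̄ = 0.4334, sum of squares 0.3415, noncentrality 11.5, power 0.78.

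**5. Both tests together.** These are simulated draws from that distribution, at 0.05. *Gated* means that the interaction and the 2-week difference are both significant. *Gated or main effect* also counts a significant group main effect (averaged over all five visits) when the interaction is not significant. *Adjusted* is the ungated 2-week contrast with baseline as covariate, variance (2/n)(1−r²).

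| r | Profile | Direct | Gated | Gated or main effect | Adjusted |
|---|---|---|---|---|---|
| 0.3 | sustained | 0.90 | 0.72 | 0.92 | 0.92 |
| 0.3 | fading | 0.90 | 0.58 | 0.87 | 0.92 |
| 0.5 | sustained | 0.90 | 0.83 | 0.90 | 0.96 |
| 0.5 | fading | 0.90 | 0.72 | 0.86 | 0.96 |
| 0.7 | sustained | 0.90 | 0.893 | 0.90 | 0.995 |
| 0.7 | fading | 0.90 | 0.86 | 0.89 | 0.995 |

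At r = 0.814, gated power is 0.897 (sustained) and 0.896 (fading), so nothing material is lost.

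**6. Robustness.** With 35 per arm, a Hotelling F test for the interaction, a t-test at 2 weeks, five effect profiles, and AR(1) correlations of 0.5 and 0.7 added to the exchangeable ones, gated power at 0.05 runs from 0.52 to 0.90, against 0.90 ungated.

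**7. The threshold kept apart.** With 35 per arm and no gate, moving from 0.05 to 0.01 alone lowers power from 0.90 to 0.74. That loss belongs to the Bonferroni rule, not to the interaction condition.

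**The case against.** A reader might infer that the 2-week difference will be examined only if the interaction is significant, so that the trial has already lost its planned power. The text does not support that. The unconditional 2-week comparison stands in the same section and matches the comparison used for sizing. On that route no power is lost to the interaction rule.

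A reader might also infer that a non-significant interaction means the intervention will be declared ineffective. That is not stated either. The GEE includes an intervention term, and analysts ordinarily turn to the main effect when there is no interaction. Counting that as success brings power to 0.86 to 0.92 in the table. This objection stands in part: the fallback answers whether the groups differ on average over the visits, which is not the 2-week contrast, and the protocol does not spell it out.

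Three points bear on the size.

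- The only related figure in the document is the OMMP retest reliability of 0.814, at which the loss vanishes. It is better read as an upper guide, since correlation over months and across treatment is likely to be lower.
- The first three measurements are planned for the ward, so week-2 completion may exceed 80%. With all 42 per arm and r = 0.5, gated power is 0.92 (sustained) or 0.84 (fading), against 0.95 ungated.
- The 4 degrees of freedom are inferred from five categorical visits. The protocol says only that an interaction will be assessed.

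Ranking of analyses is often left to a statistical analysis plan, which is not shown here. But the article itself states both routes and the conditional rule, so the conflict lies in what it fixes.

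**Conclusion.** The concern holds as an unresolved choice with a possible cost in power. The protocol sets out two routes to the 2-week pain difference and does not name the deciding one, while the Abstract points to the GEE. If the GEE route decides, power at 0.05 for the contrast sized at 90% is 0.58 to just under 0.90, given 33.6 completers per arm, exchangeable correlations of 0.3 to 0.7 and the two profiles above. The loss is largest when correlation is low and the effect fades, and negligible near r = 0.8. If the direct comparison decides, the rule costs nothing at 2 weeks and affects only the 1-week, 1-month and 6-month differences. A definite power loss is therefore not shown. What is shown is that the plan leaves open which rule applies.

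**What to change.** State that the primary analysis is the single-degree-of-freedom group difference in OMMP score at 2 weeks. Estimate it from the GEE with the baseline OMMP score as a covariate and the post-baseline visits as outcomes. Report it with its confidence interval whatever the interaction P value.

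Make the interaction test and the 1-week, 1-month and 6-month contrasts secondary. Keep the separate unadjusted 2-week comparison if wanted, but label it supportive, so that only one test decides. State the significance level of the primary test explicitly and reconcile it with the 0.05 used for sizing.

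The cost is a few sentences in the analysis section. The data and software are unchanged. Under the same assumptions, the baseline-adjusted contrast has power of about 0.92 to 0.995 at 0.05. The gain over 0.90 comes from the covariate, not from removing the condition.

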**Methods:**

This is an assessor-blinded randomized controlled trial following the SPIRIT guidance. A total of 84 depressed patients will be recruited from the inpatient wards of a psychiatric hospital and randomly assigned to the control and experimental groups. Patients in the control group will be treated as usual. In contrast, patients in the experimental group will receive 6 sessions of the PPSF intervention for two weeks on top of the routine care. Primary outcomes are psychological pain, hope, cognitive distortions. Secondary outcomes are depression and suicidal ideation. Data will be collected at 5-time points: baseline, 1 and 2 weeks (post-intervention), 1 month (follow up), and 6 months after baseline. Generalized equation evaluation will be used to assess the effectiveness of the PPSF intervention.

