### Data collection

The data collection for this study will be independently accomplished by a trained nurse who will be blind to recruitment and allocation. The study will measure outcomes at 5 time points: baseline, 1 and 2 weeks (post-intervention), and 1 month and 6 months after baseline (follow-up). The schedule of the study is shown in Table 2. As depressed inpatients are commonly hospitalized for 2–3 weeks, the first 3 measurements will be handed out on the spot in the ward, filled in, and collected. The last 2 measurements will be collected by appointment with patients in the outpatient clinic. All questionnaires will be issued in paper form and will be archived by special researchers after collection. If patients leave the wards earlier than 3 weeks, they will not be allowed to complete the questionnaire 3 times in the ward, and data collection will be completed by appointing patients to the outpatient clinic. Participants in the control group will also be required to complete the measurements at the same time points.

**Table 2 Tab2:** Schedule of enrolment, intervention, and outcome assessment

**Timepoint**	**Enrolment**	**Allocation**	**Post-allocation**				**Filler**
	-T_1_	T_0_ baseline	T_1_ 1st week	T_2_ 2nd week	T_3_ 1st month	T_4_ 6th month	

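### The P < 0.01 threshold is not tied to one named set of five tests, and it conflicts with a sample size calculated at two-sided 0.05

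*Protocol article*

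**What the plan says.** The abstract names three primary outcomes ("Primary outcomes are psychological pain, hope, cognitive distortions") and two secondary ones ("Secondary outcomes are depression and suicidal ideation"), so there are five outcomes. Each is measured at baseline and at four later times.

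The Data analysis section then plans, for every outcome:

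- a between-group comparison, with no test named: "This study will compare the differences in primary and secondary outcomes between the two groups at two time points", these being baseline and 2 weeks;
- a GEE over all five time points with time, intervention and interaction effects;
- time-specific comparisons that depend on the interaction: "When there is an interaction effect, then the analysis of the simple effects will be adopted".

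On multiplicity the section says "Bonferroni correction will be used for multiple comparisons, that is, dividing 0.05 by the number of comparisons" and concludes that P < 0.01 is significant. It does not give the number of comparisons or say what is counted.

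The Sample size and recruitment section uses psychological pain only, with d = 0.788, two-sided alpha 0.05 and power 0.90. This gives 35 per group, raised to 42 for dropout.

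**The concern.** A Bonferroni threshold protects only the family of tests it was divided by. Here the divisor is left to inference, and the tests listed beside it form more than one possible family. The 2-week treatment effect can be reached by two routes: directly, or through the GEE after a significant interaction. If the decisive route is not fixed in advance, the favourable one can be chosen after the data are seen, and the promised 5% no longer holds.

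The second issue is internal consistency. Alpha is 0.05 where the trial is sized and 0.01 where it is judged, so the stated 90% power does not describe the analysis that will decide the result.

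**Working it through.** **1. The threshold.** 0.05 / 0.01 = 5, so five comparisons are implied. Candidate families:

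- Five outcomes, one 2-week comparison each: k = 5, threshold 0.01. Fits.
- Five outcomes, one GEE interaction test each: k = 5, threshold 0.01. Fits.
- Five time points: k = 5, but this counts baseline, where no treatment effect can exist.
- Three primary outcomes at one time: k = 3, threshold 0.05 / 3 = 0.0167. Does not fit.

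So 0.01 is a correct divisor for either of the first two sets taken alone: 5 × 0.01 = 0.05 at most, and 1 − 0.99^5 = 0.049 if the tests are independent.

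**2. Both sets together.** If significance by either route counts, there are 10 tests at 0.01, and the Bonferroni bound is 10 × 0.01 = 0.10. The actual error depends on correlations that the article does not give. I simulated it under no effect anywhere, with 35 per arm, within-person correlation 0.5, between-outcome correlation 0 to 0.7 (all assumed) and known-variance Wald tests:

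| What counts as a positive result | Family-wise error |
|---|---|
| Interaction tests alone, five outcomes | 3.6-5.0% |
| Interaction test or 2-week comparison, five outcomes | about 7-9% |
| The same, plus the GEE intervention main effect | about 9-12% |
| Interaction test or 2-week comparison, three primaries only | about 5-6% (bound 6 × 0.01 = 6%) |

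**3. Simple effects.** With no effect anywhere, gated simple effects cannot exceed the error of their gate, and in simulation they give only about 1%. The gate protects less when an effect exists at some times only. With a true effect of 0.788 SD at 2 weeks and none elsewhere, the chance of at least one false claim at another post-baseline time is about 8-12% over five outcomes, under the same assumed correlations.

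**4. Power.** First, the plan's own figures:

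- Pooled SD = √[(0.98² + 1.05²) / 2] = 1.016, so d = (2.3 − 1.5) / 1.016 = 0.788, as stated.
- Two-sample t-test with 35 per group: 68 degrees of freedom, noncentrality 0.788 × √(35/2) = 3.30.
- At two-sided 0.05, power = 90.1%. The 35 per group is reproduced.

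With only alpha changed to 0.01:

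- 35 per group: 73.9%.
- 42 per group (no dropout at all): 83.2%.
- 90% power at 0.01 needs 50 per group before dropout.

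**The case against.** The strongest defence is that five has a natural meaning: five outcomes, one test each. This stands. On that reading, with one route named, 0.01 is valid, so the article does not show that type I error control fails. It leaves the control undefined.

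The 2-week comparison may also be meant as a contrast from the GEE, since no separate test is named for it. That is possible. But it is introduced without condition, while GEE simple effects follow only after an interaction, so the text would then disagree with itself on whether the 2-week contrast is conditional. Either way the ranking has to be written down.

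A statistical analysis plan, not shown here, could name the family. It could not remove the mismatch in the article between an alpha of 0.05 for sizing and 0.01 for inference.

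Two stronger readings are tempting and not supported:

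- A reader might count three primaries at four post-baseline times (12 tests) or five outcomes at four times (20 tests) and infer errors of 1 − 0.99^12 = 11.4% or 1 − 0.99^20 = 18.2%. Those figures assume that every contrast is tested unconditionally. The article opens simple effects only after an interaction.
- A reader might take the primary hypothesis, which lists the three primary outcomes together, as requiring all three to succeed, and infer much lower power. The Hypotheses section states expected directions and no such success rule. The effect size of 0.788 is given for psychological pain only.

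**Conclusion.** The point holds in a limited form. The 0.01 threshold is arithmetically sound for one test on each of five outcomes, but the article lists two such sets and does not say which decides. If either may decide, family-wise error over five outcomes is about 7-9% instead of 5%. That range rests on the assumed correlations, while the 10% ceiling does not. Over the three primaries alone the excess is slight.

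The power conflict needs no assumption beyond the plan's own d and group size: 73.9% at the threshold the trial will use, against the 90% stated. Both matters should be settled before any unblinded analysis, because they define what counts as a positive trial.

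**What to change.** In the Data analysis section:

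1. Name the 2-week between-group contrast from the GEE as the single confirmatory test for each primary outcome. Estimate it whatever the interaction test shows, and drop the separate 2-week comparison.
2. Test OMMP, the outcome on which the trial is sized, first at two-sided 0.05. Test hope and cognitive distortion only if OMMP is significant, either in a pre-stated order or with Bonferroni or Holm between the two.
3. Report the other time points and the secondary outcomes as supportive estimates with 95% confidence intervals.

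This holds family-wise error over the primary outcomes at 5%, and the alpha for OMMP again matches the sample size calculation.

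If the sponsor prefers to keep 0.01, state that the family is the five outcomes with one named test each, and restate the power as about 74% at 35 per group.

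The cost is wording only, with no change to data collection. The downside of the first option is small: no confirmatory claim can be made on hope or cognitive distortion if OMMP fails.

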#### Suicidal ideation

Suicidal ideation will be measured using the Self-Rating Ideation of Suicide Scale(SSIOSS) [51], which contains 26 items and 4 factors. The four factors are optimism, despair, masking, and sleep, and each entry is scored as “yes” or “no”. Suicidal ideation score was obtained by adding the scores of optimism factor, despair factor and sleep factor, and the higher the score, the stronger the suicidal ideation. The total score on the scale is 26, and a score of ≥ 12 indicated that the patient had suicidal ideation. The Chinese scale has the Cronbach’s α coefficient of 0.86 and the re-test reliability of 0.87 in undergraduates [51].

It should be explained that we did not include suicidal ideation in the outcomes when we registered at Chinese Clinical Trials.gov. However, later, we decided to add suicidal ideation as a secondary outcome, considering the strong relationship between psychological pain and suicide.

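### The flat Bonferroni level of P < 0.01 is valid but needlessly conservative: Holm's step-down procedure over the same comparisons keeps the same 5% family error and is never less powerful

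*Protocol article*

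**What the plan says.** The Abstract ranks the outcomes: "Primary outcomes are psychological pain, hope, cognitive distortions. Secondary outcomes are depression and suicidal ideation". The Data analysis section of the protocol article then gives one multiplicity rule for everything: "Bonferroni correction will be used for multiple comparisons, that is, dividing 0.05 by the number of comparisons". It concludes that P < "0.01 represents a statistically significant difference". No step-down or ordered procedure is mentioned, and primary and secondary outcomes are not treated differently.

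The section does not say what is being counted. A divisor of five fits the three primary plus two secondary outcomes. It also fits the measurement schedule: "The study will measure outcomes at 5 time points". The same paragraph describes a two-week comparison, GEE effects of time, group and their interaction, and conditional follow-up tests: "When there is an interaction effect, then the analysis of the simple effects will be adopted".

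**The concern.** Single-step Bonferroni holds every comparison to the strictest level, 0.05/k, however many of the others have already been shown to be non-null. Once one null hypothesis has been rejected, at most k − 1 true nulls remain, and 0.05/(k − 1) would be enough for the next. Bonferroni ignores this. A real effect can therefore be missed at P between 0.01 and 0.05 although the 5% family error did not require it.

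This matters in a trial with 42 patients per arm before dropout that will make several claims. A rule that leaves power unused makes a true effect on pain, hope or cognitive distortion harder to show, and gives no better control of the family error in exchange.

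**Working it through.** **Inputs from the protocol article (Sample size and recruitment).** Means and SDs 1.5 ± 0.98 and 2.3 ± 1.05; two-sided α = 0.05; power 0.90; 35 per group, raised to 42 for 20% dropout.

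**Inputs assumed, because the article does not give them.** Effect sizes for hope, cognitive distortion, depression and suicidal ideation; the correlation between outcomes (0.3 to 0.7, equal for all pairs); one two-sample t-test per outcome; and the reading that the five comparisons are the five outcomes.

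**Step 1: reproduce the plan's own figures.**
- d = (2.3 − 1.5) / √((0.98² + 1.05²)/2) = 0.8/1.0156 = 0.788, as stated.
- Noncentral-t power with 35 per group at two-sided 0.05 is 0.901, and with 34 it is 0.893. So 35 per group reproduces.
- 0.05/5 = 0.01, as printed.
- Evaluable per arm after 20% loss: 42 × 0.8 = 33.6, taken as 34. At 34 per arm, power is 0.893 at 0.05 and 0.72 at 0.01.

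**Step 2: why Holm is never worse.** Order the P values and compare the smallest with 0.05/k, the next with 0.05/(k − 1), and so on up to 0.05, stopping at the first failure. For k = 5 the levels are 0.01, 0.0125, 0.0167, 0.025 and 0.05.
- *Power:* every level is at least 0.05/k. The P values at or below 0.05/k come first in the order, so all of them are rejected. Everything Bonferroni rejects, Holm rejects.
- *Family error:* let m of the k nulls be true. When the first true null is reached, at most k − m hypotheses have been rejected, so its level is at most 0.05/m. By the union bound the chance of any false rejection is at most m × 0.05/m = 0.05. No assumption about correlation is used.

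This argument holds for any k and for any set of comparisons.

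**Step 3: size of the gain.** Simulation with 40,000 trials per scenario, 34 per arm, five outcomes, correlation 0.3 to 0.7:

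| True effects | Power measured for | Bonferroni at 0.01 | Holm over five |
|---|---|---|---|
| All five d = 0.788 | each outcome | 0.72 | 0.81-0.83 |
| Three primaries 0.788, secondaries 0 | each primary | 0.72 | 0.76-0.77 |
| Pain 0.788, other four 0.5 | pain | 0.72 | 0.73-0.75 |
| Pain 0.788, other four 0.5 | hope, distortion | 0.28-0.29 | 0.36-0.38 |
| Pain 0.788, other four 0 | pain | 0.72 | 0.72 |

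Family error was at or below 0.048 in every scenario with a true null. The pattern follows from Step 2: Holm gains only when other hypotheses in the family are also rejected.

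**Step 4: primary-first testing, for comparison.** Here Holm is applied to the three primaries at 0.05, and the secondaries are tested only if all three are rejected. Power per primary is 0.85-0.86 if all five outcomes have d = 0.788, and 0.78-0.79 for pain if only pain responds. If one primary has no true effect and the other four outcomes do, power for a real secondary effect falls from about 0.72 under the flat rule to about 0.03.

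**The case against.** The strongest objection is that nothing here is wrong. Bonferroni is valid under any correlation and keeps the family error at or below 5%. That stands: this is a point about efficiency. It remains worth raising because the article fixes the rule and the threshold explicitly, and a replacement exists that never rejects less.

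Three stronger readings are tempting, and the article does not support them.

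- *A reader might infer that the two secondary outcomes, one of them added after registration ("later, we decided to add suicidal ideation as a secondary outcome"), take two fifths of the 5% error from the primaries.* That needs the five comparisons to be the five outcomes. The reading is plausible, because five time points include baseline, where a group difference is not a treatment effect. But the article does not say so. If the correction runs over time points within each outcome, the secondaries take nothing from the primaries.
- *A reader might infer that the primaries lose about 9 to 14 points of power.* That range requires d = 0.788 for all five outcomes, and its upper end also requires primary-first testing. The article gives this effect for psychological pain alone. With Holm over the five, the gain for pain can be zero.
- *A reader might infer that the primaries ought to be tested first.* That is a trade-off. The flat rule lets depression and suicidal ideation be claimed independently, whereas the gate largely gives those claims up when any one primary fails.

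It is also fair to say that sizing at 0.05 while judging at 0.01 is the larger problem: with 35 per group, power is 0.74 and not 0.90. That is a separate point. Holm recovers part of that loss under some scenarios and none under others.

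**Conclusion.** The point holds as an avoidable inefficiency in a stated rule. That Holm is at least as powerful as Bonferroni at the same family error is a mathematical fact and does not depend on how the comparisons are counted. Its size is conditional: from no gain for psychological pain when only pain responds, through about 4 points per primary when only the primaries respond, to 9-11 points per outcome (0.72 to 0.81-0.83) when all five have d = 0.788. These figures rest on 34 evaluable per arm, assumed correlations of 0.3 to 0.7, one t-test per outcome, and the five comparisons being the five outcomes. They should be read as a range, not as the loss this trial will suffer. The 5% guarantee, under either method, covers only the comparisons that are counted. If simple-effects tests at several time points also support claims, they belong in the family.

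**What to change.** In the Data analysis section, first list the five comparisons, with one test for each (outcome, time point or model term). Then replace the flat P < 0.01 by wording such as:

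> The five comparisons listed above are tested with the Holm step-down procedure at a two-sided family level of 0.05. Their P values are ordered from smallest to largest and compared in turn with 0.05/5, 0.05/4, 0.05/3, 0.05/2 and 0.05; testing stops at the first that is not significant.

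If the count turns out not to be five, the same wording applies with that number. The list must come with the change: if 0.01 was meant to protect several time points, removing it without naming the family would remove that protection.

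The cost is a few lines of text, settled before the data are unblinded, with no added patients or data and no loss of power for any outcome. If the sponsor would rather put the primaries first, that can be chosen deliberately, with the near-loss of the secondary claims after a failed primary stated in the plan.

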### Participants

#### Inclusion criteria

Patients meeting the following criteria will be included: (1) meet the ICD-10 diagnostic criteria for depression; (2) are aged 18–60 years; (3) have depression scores ≥ 20 measured as measured using the 24-item Hamilton Rating Scale for Depression (HAMD-24); (4) have psychological pain scores ≥ 123 as measured using the Orbach & Mikulincer Psychological Pain Scale (OMMP); (5) consent to participate, and (6) can communicate and express themselves with the researchers. We changed the original inclusion criteria from “ ≥ 136” to “ ≥ 123” for OMMP scores because a later cross-sectional study on psychological pain in depressed patients conducted by our team showed that when the OMMP was ≥ 123, it suggested that patients might have suicidal tendencies.

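### The single P < 0.01 threshold also governs a worsening of suicidal ideation, where a correction meant to limit false claims of benefit makes a harm signal harder to flag

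*Protocol article*

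**What the plan says.** The Data analysis section of the protocol article covers all five outcomes with the same methods. For the contrast of baseline with week 2 it states: "This study will compare the differences in primary and secondary outcomes between the two groups at two time points". For the longitudinal analysis, "the GEE model will be performed to compare the trends of primary and secondary outcomes at different time points", over baseline, 1 week, 2 weeks, 1 month and 6 months. Simple effects are examined only when there is an interaction. On multiplicity, "Bonferroni correction will be used for multiple comparisons, that is, dividing 0.05 by the number of comparisons". The section then closes: "Thus, *P* < 0.01 represents a statistically significant difference". That sentence has no limit by outcome or by direction of effect.

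Suicidal ideation falls inside this scope. The abstract lists three primary outcomes ("Primary outcomes are psychological pain, hope, cognitive distortions") and two secondary ones, depression and suicidal ideation. The Suicidal ideation section explains the addition: "we decided to add suicidal ideation as a secondary outcome, considering the strong relationship between psychological pain and suicide". A higher SSIOSS score means stronger ideation, and the Hypotheses section foresees only a reduction.

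Two other places give context. The Inclusion criteria section justifies the OMMP entry cut-off because "when the OMMP was ≥ 123, it suggested that patients might have suicidal tendencies". The Ethical considerations section regards adverse effects as unlikely and sets up no data monitoring committee.

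**The concern.** The protocol gives the purpose of the correction as reducing type I error. With five outcomes all expected to improve, that means limiting false claims that PPSF works. For a deterioration the costly mistake is the opposite one, a miss, and a stricter threshold makes a miss more likely.

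This matters most for suicidal ideation. The entry cut-off was chosen with suicidal tendencies in mind. In the text shown, the SSIOSS is the only suicide-specific measure compared between arms. The interaction condition adds to the problem. If the interaction test is also read at 0.01, differences at week 1, month 1 and month 6 may not be examined at all.

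The Conclusion section foresees hospital use of PPSF if it proves effective. A statement of no significant difference in suicidal ideation would support that step, and here it could rest on a threshold chosen for another purpose.

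**Working it through.** **1. Reproduce the plan's threshold.** Bonferroni: 0.05/k. The protocol does not state k. With k = 5, 0.05/5 = 0.01, which matches. Five outcomes and five time points both fit, so k = 5 is an inference.

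**2. Does the rule reach a worsening of the SSIOSS?** The tests cover primary and secondary outcomes, suicidal ideation is secondary, and the closing sentence is unqualified. So a difference against PPSF with 0.01 ≤ P < 0.05 is, by the written rule, not statistically significant.

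**3. Inputs for the size.**
- From the Sample size and recruitment section: 42 per arm and 20% dropout. After dropout, 42 × 0.8 = 33.6, taken as 34 per arm.
- Assumed: true worsening of 0.3 to 0.6 SD; two-sided tests (the Data analysis section does not state sidedness, while the sample size calculation is two-sided); a two-sample t-test in place of the GEE contrast.

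**4. Smallest observed worsening that is flagged**, d = t_crit × √(2/n), with 2n − 2 degrees of freedom:
- n = 42: at 0.05, 1.989 × √(2/42) = 0.43 SD; at 0.01, 2.637 × √(2/42) = 0.58 SD.
- n = 34: at 0.05, 1.997 × √(2/34) = 0.48 SD; at 0.01, 2.652 × √(2/34) = 0.64 SD.

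With 42 per arm, an observed worsening between about 0.43 and 0.58 SD is where the two thresholds disagree.

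**5. Chance of flagging a true worsening**, from the noncentral t distribution with noncentrality d × √(n/2):

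| True worsening (SD) | n = 42, 0.05 | n = 42, 0.01 | n = 34, 0.05 | n = 34, 0.01 |
|---|---|---|---|---|
| 0.3 | 27% | 11% | 23% | 9% |
| 0.5 | 62% | 37% | 53% | 29% |
| 0.6 | 78% | 55% | 68% | 43% |

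**6. Price of relaxing the threshold for harm.** With no true difference, the chance of a false alarm against PPSF at one visit is 0.05/2 = 2.5% instead of 0.01/2 = 0.5%. Over the four post-baseline visits the upper bounds are 4 × 2.5% = 10% and 4 × 0.5% = 2%. If the visit statistics are multivariate normal with an assumed common correlation of 0.5 to 0.7, the chance of at least one false alarm is about 7.8% to 6.5% instead of 1.7% to 1.5%.

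**The case against.** The strongest reply is that nothing here is misstated. The protocol defines suicidal ideation as an efficacy outcome with a hypothesised reduction, and one adjusted threshold across efficacy outcomes is ordinary practice. It never calls the SSIOSS a safety outcome, and a condensed article may leave harm analyses to a fuller document. The loss of power is the generic result of moving from 0.05 to 0.01 and would hold for any outcome. All of this stands, and it limits the weight of the point. It does not remove it, because the article does not leave the threshold open. It states a rule without exception, and a later plan with another threshold for harm would depart from it.

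Three stronger readings are tempting and are not supported:
- *That the plan would conceal a worsening.* The rule only decides what is called significant. Nothing prevents the estimate, interval and P value from being reported, and nothing says that P = 0.02 in the wrong direction would be read as absence of harm.
- *That suicidality would go unnoticed during the trial.* Usual care, given to both arms, includes suicide risk assessment by ward nurses, and progress is reported to the ethics committee every three months. These are not between-arm comparisons, but recognition does not depend on the final P value alone.
- *That leaving the cut-off unused is an error.* The statement that "a score of ≥ 12 indicated that the patient had suicidal ideation" belongs to the description of the scale. Analysing the score without dichotomising it is a legitimate choice, and the plan contains no test of proportions above the cut-off.

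It is also possible that the correction was meant only for the comparisons that follow a significant interaction. The closing sentence would then be wider than intended and would still need a qualifier.

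**Conclusion.** The point holds as an improvement to a stated rule. As written, a worsening of suicidal ideation on PPSF with P between 0.01 and 0.05 would be labelled not significant. With 42 per arm, the chance of flagging a true worsening of 0.3 to 0.6 SD is 11–55% under the rule, against 27–78% at the conventional level. At 0.5 SD about a quarter of trials (62% − 37% = 25%) would fall between the two thresholds.

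These sizes depend on the assumed worsenings, two-sided testing and the t-test approximation to the GEE. The existence of the gap depends only on the protocol's own sentences. No figure in the protocol is shown to be wrong.

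**What to change.** Add to the Data analysis section text to this effect:

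*The Bonferroni threshold applies to claims of benefit. For suicidal ideation, the between-arm difference in SSIOSS score at each post-baseline visit will be reported with an unadjusted 95% confidence interval, whether or not the interaction is significant. An interval that excludes zero in the direction against PPSF will be described as a possible harm signal.*

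The same sentence could cover HAMD-24, since worsening depression falls under the same rule. A table of patients at or above the SSIOSS cut-off by arm and visit is optional.

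The cost is two or three sentences and one table from data already scheduled for collection. The efficacy threshold does not change. The downside is the higher false-alarm rate in the harm direction: 2.5% instead of 0.5% per visit, and at most about 10% instead of 2% over four visits. The wording as a possible signal, not a finding of harm, allows for this.
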